### Participants

Three participant cohorts will be recruited: i) young healthy (n = 35); ii) older healthy (n = 35); and iii) spinal cord injured (SCI, n = 35). Sample size calculations were performed using Gpower (Gpower 3.1) with an effect size f = 0.4 for a repeated-measure ANOVA [parameters: within-between interaction; α = 0.05; β = 0.80; 3 groups; 3 measurements (i.e. peak hyperaemia at 38, 24, 16°C)], based on published data on the mean difference in peak hyperaemia (expressed as percentage of maximal cutaneous vascular conductance, CVCmax) during control conditions (32.7 ± 9.4% CVCmax) and during sensory nerve block (17.3 ± 6.8% CVCmax) [27]. Changes in peak hyperaemia were identified as the primary experimental outcome, as this represents a robust and repeatable microvascular response. The effects of cooling on peak hyperaemia are likely to be similar to those of cutaneous sensory nerve bloc [27], given that cooling also impairs the activity of cutaneous sensory nerves [28]. Hence, it was identified that the 50%-reduction in peak hyperaemia reported by Lorenzo and Minson [27] was a large (f = 0.4) and physiologically meaningful effect size to evaluate the beneficial effects of cooling on sustained mechanical loading. Based on the data above, we estimated a minimum sample size of 18 participants per group, and we propose testing of 35 individuals per group to allow for sufficient statistical power and to account for up to 50% dropout. Participants will be recruited according to the criteria in Table 1.

**Table 1 pone.0303342.t001:** Participant inclusion and exclusion criteria.

Inclusion	Exclusion
18–70 years old (young healthy 18–35 years old; older healthy 55–70 years old).	Young and older health groups only (does not apply to SCI group, see text below): suffering from cardiovascular, metabolic, and neurological disorders and/or comorbidities, e.g., hypertension, diabetes, chronic lung disease.
Male or female (minimum 17 for each sex).	Raynaud’s disease.
Skin tone dark, medium, or light (minimum 11 for each tone—assessed via the Fitzpatrick Scale [29]).	Suffering from skin conditions (e.g., eczema).
Healthy groups only: physically active (i.e., performing exercise 1 to 3 times a week).	Under drug therapy affecting thermoregulation (e.g. muscarinic antagonists).
SCI group only: presenting thoracic injury/paraplegia (i.e., injury level within T1-S1).	Smoker or Vaper.
SCI group only: >12 months post-injury and no history of PUs.	

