### Statistical analyses

Data will be assessed for normality of distribution (Kolmogorov—Smirnov test), and then analysed for the independent and interactive effects of pressure stimuli’s temperature (i.e. 3 levels: 38, 24, 16 °C), and of participant group (i.e. 3 levels: young, older, SCI) on within- and between-subject mean differences in peak hyperaemia (N = 35 with 95% Confidence Intervals). This will be conducted using a 2-way mixed model ANOVA or Friedman, depending on the data distribution (parametric or non-parametric, respectively). Post-hoc analyses will be performed between pressure stimuli’s temperatures and participant groups based on the presence of main effects and using Tukey’s test. The use of regression models will evaluate the relationship between absolute cooling temperatures and peak hyperaemia during pressure stimuli. This approach is designed to identify “physiological thresholds” for the protective effects of cooling under mechanical loading. Mean thresholds will subsequently be determined and their inter-individual variability across the cohort. For the perceptual data, thermal discomfort will identify “Uncomfortable” on the Likert Scale as the threshold onset of discomfort. Regression analyses will be used to interrogate the relationship between pressure stimuli’s cooling temperature and local discomfort, for each participant. This approach will also enable the assessment of “perceptual cooling thresholds” for cold-induced discomfort at two absolute cold temperatures (i.e. 24 and 16 °C), and their individual variability. Physiological and perceptual thresholds will be combined to produce common cooling parameters that will accommodate different cooling characteristics. Regarding the secondary experimental outcomes, these will be within- and between-subject changes in biomarkers’ expression, skin structural and biophysical properties (i.e. imaging parameters and skin friction), and subjective thermal perceptions, as a function of pressure stimuli temperature (i.e. 3 levels: 38, 24, 16°C), time (i.e. varying levels depending on variables’ sampling rate), and of participant group (i.e. 3 levels: young, older, SCI). Data will be first assessed for normality of distribution (Kolmogorov—Smirnov test), and then analysed for the independent and interactive effects of pressure and stimuli temperature, time, and participant group by means of a 3- way mixed model ANOVA (or Friedman). Post-hoc analyses will be performed between pressure stimuli temperatures, time, and participant groups based the presence of main effects and using Tukey’s test. Group-related co-variables associated with sex, skin tone, and clinical status (applicable to SCI participants only, e.g. rehabilitation status) will be considered in all analyses to interpret the proportion of variance unexplained by the main effects (i.e. temperature, time, and group) and their interactions.

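### Post-hoc comparisons are tied to main effects, so a significant temperature-by-group interaction, the effect the trial is sized on, is not traced to a group or a cooling level

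*Protocol article*

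**What the plan says.** All references are to the Protocol article.

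- **Statistical analyses, primary outcome.** Peak hyperaemia is to be "analysed for the independent and interactive effects of pressure stimuli" temperature and participant group in a two-way mixed ANOVA (or Friedman). Post-hoc tests then compare temperatures and "participant groups based on the presence of main effects and using Tukey" (the test named is Tukey's).
- **Statistical analyses, secondary outcomes.** The three-way models carry the same rule, with time added: "time, and participant groups based the presence of main effects and using Tukey".
- **Meaning of the term.** The closing sentence of that section speaks of variance "unexplained by the main effects (i.e. temperature, time, and group) and their interactions". Main effects are thus listed as temperature, time and group, and interactions are named separately.
- **Participants, sample size.** The calculation is run "with an effect size f = 0.4 for a repeated-measure ANOVA", and its first listed setting is "within-between interaction".
- **Introduction, second aim.** The study is to find out how ageing and SCI change the pathways through which cooling helps.

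**The concern.** The second aim is an interaction question: does the effect of cooling differ between young, older and SCI participants? The trial is sized for that term and the ANOVA tests it. The follow-up rule, however, is attached to the other terms.

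A Tukey comparison after a main effect compares marginal means. Groups are averaged over the three temperatures, and temperatures are averaged over the three groups. Neither comparison estimates how the cooling effect differs between groups.

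If the interaction is significant, a team following the rule would know that the groups differ somewhere in their response but would have no planned estimate of where. It would also report pooled temperature differences, which are hard to interpret in that situation. The Discussion intends the results to inform device design for at-risk people, so the answer for the SCI group matters in itself. If the contrasts are not fixed in advance, they will be chosen after the interaction has been seen.

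**Working it through.** **Step 1: the text.** The sizing term is the interaction, the tested terms are main effects and interaction, and the stated trigger for follow-up is main effects. The section's own list keeps interactions apart from main effects, so the trigger cannot comfortably be read to include them. The planned regressions describe thresholds for each participant and their variability across the cohort. They do not compare cooling effects between groups.

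**Step 2: what the marginal comparisons estimate.** The plan gives no cell means, so an illustration is needed.

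- From the Participants section: control 32.7 ± 9.4 and nerve block 17.3 ± 6.8 (% CVCmax). Difference 32.7 - 17.3 = 15.4. Pooled SD = √((9.4² + 6.8²)/2) = √67.3 = 8.2.
- Assumed: 24°C gives half of the 16°C effect; young and older have the full effect; SCI has half; all groups share the same 38°C mean, set to 0.

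| Group | 38°C | 24°C | 16°C | Mean over temperatures |
|---|---|---|---|---|
| Young | 0 | -7.7 | -15.4 | -7.7 |
| Older | 0 | -7.7 | -15.4 | -7.7 |
| SCI | 0 | -3.85 | -7.7 | -3.85 |

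Pooled 16-versus-38 difference: (-15.4 - 15.4 - 7.7)/3 = -12.8. This holds for no group. It overstates the SCI effect by 67% (12.83/7.7 = 1.67) and understates the other two by 17% (12.83/15.4 = 0.83).

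The SCI-minus-young difference in the 16-versus-38 effect is -7.7 - (-15.4) = 7.7. The marginal SCI-minus-young difference is -3.85 - (-7.7) = 3.85. Now move the whole SCI row and leave its cooling effect alone:

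- SCI up by 4: marginal difference 3.85 + 4 = 7.85.
- SCI down by 3.85: marginal difference 3.85 - 3.85 = 0.

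The difference in cooling effect is 7.7 throughout. The quantity that triggers and feeds the group comparison runs from 0 to 7.85, so it does not measure what the second aim asks.

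**Step 3: how often the group comparison would be skipped.** Simulation with 8,000 trials per setting, SD 8.2, and equal correlation between temperatures (assumed 0.3, 0.5, 0.7, as none is given). Tests at 0.05: group MS over between-person MS; temperature MS and interaction MS over residual MS. At 35 per group the degrees of freedom are (2, 102), (2, 204) and (4, 204).

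35 per group, correlation 0.3 / 0.5 / 0.7:

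| SCI mean at 38°C | Interaction significant | Interaction significant, group main effect not |
|---|---|---|
| Equal to others | 87% / 97% / 99.9% | 18% / 30% / 40% |
| 4 points higher | 87% / 96% / 99.9% | 0% / 0.1% / 0.3% |
| 3.85 points lower | 88% / 97% / 99.9% | 83% / 92% / 95% |

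In the last row the group means are exactly equal, so the group test misses 95% of the time and the ceiling is 0.95 × 0.999 = 0.95. Simulation error can lift a run to 96%. In every setting the temperature main effect was significant in 100% of trials.

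The derivation of the plan's own minimum of 18 per group does not enter this check.

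**The case against.** Several points on the other side stand.

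- **The interaction test is itself a between-group comparison of the cooling effect.** This is correct. A reader might infer that the plan makes no between-group comparison of cooling at all. The text does not support that, because the overall test is planned. What is missing is the step after it.
- **A reader might infer that a significant interaction could be followed by no post-hoc test whatever.** That requires a pure crossover with no overall cooling effect. It conflicts with the roughly 50% reduction that the Participants section expects. In the scenarios above, temperature comparisons were triggered every time.
- **The section does not say that follow-up is limited to main effects, and an unseen analysis plan may add contrasts.** This is fair as far as it goes. But the article does more than leave the matter open: it states a trigger, states it twice, and names no other. The between-subject mean differences with confidence intervals mentioned in the same section are not defined as differences in the cooling effect.
- **The percentages are fragile.** They are. They depend on the SCI level at 38°C, on the half-effect assumption and on the correlation, none of which is stated. The inputs are % CVCmax figures, whereas the Skin blood flow section defines the primary outcome as percentage change from baseline flow.
- **Two further criticisms are tempting but unsupported.** One is that the group main effect is always the weakest test. With the SCI mean 4 points higher at 35 per group, its power is about 100%, against 87% and 96% for the interaction at correlations 0.3 and 0.5. The other is that Tukey's procedure would use an unsuitable error term. The article states neither the error term nor unequal covariances.

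**Conclusion.** The point holds as a defect in a stated rule. The trigger for follow-up is placed on main effects in both the primary and secondary analyses, while the design and the second aim rest on the interaction. Followed as written, a significant interaction is detected but not localised, and the comparisons that are reported average over the factor that matters.

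The defect is logical and needs no simulation. Its practical frequency cannot be fixed from the article. At 35 per group with SCI at half effect, a significant interaction with a non-significant group main effect occurs in about 18% to 40% of trials if the 38°C means are equal. It occurs in anything from about 0% to about 95% if the SCI mean is about 4 points higher or lower. Even where the group comparison is triggered, it is of marginal means and does not answer the question. The change should be made; it does not put the primary test itself in doubt.

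**What to change.** Replace the post-hoc rule in both places where it appears. Suggested content:

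- From the primary mixed model, estimate 24 versus 38°C and 16 versus 38°C within each group (2 × 3 = 6 contrasts).
- Estimate the differences of these contrasts for older versus young and SCI versus young (2 × 2 = 4 contrasts).
- Report all of them with multiplicity-adjusted confidence intervals, whether or not any main effect is significant. State the adjustment and the family it covers.
- Interpret marginal comparisons of temperatures or groups only where the interaction does not contradict them.
- Apply the same principle to the three-way models for the secondary outcomes.

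The cost is analysis wording only, with no new data, visits or procedures. The downside is a few more prespecified contrasts and slightly wider adjusted intervals.

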### Experimental procedures

Once screened and recruited, participants will be invited to their pseudo-randomly allocated experimental session [31]. They will come to the laboratory wearing comfortable, loose-fitting attire. Upon arrival, participants will be seated whilst they acclimatise to the ambient conditions of the laboratory (22–24 °C; 50% RH) before recording height and body mass (Model 874; Seca GmbH, Hamburg, Germany).

Following the pre-experimental checks, participants will lie down in the prone position on a hospital bed. Care will be taken to ensure that participants are as comfortable as possible by providing pillows as necessary to support the pelvic region and upper body, given the length of time (75 minutes) they will need to remain in this position. The addition of the pillows also serves to support the lumbar region by flattening the sacroiliac joint and reducing any pronounced lordosis of the spine while lying in a prone position.

First, structural, and functional imaging of the skin of the sacral skin using Optical Coherence Tomography (OCT) will be performed. This will be followed by sampling of skin sebum at the sacrum for subsequent biomarker analysis, using an established methodology involving a 2-minute application time and tweezer extraction to avoid cross-contamination [32]. The investigator will then place a custom-built thermal probe over the sacrum and load it with a weight (see below for details) to achieve pressure of 60 mmHg. The thermal probe consists of a water-perfused set of Peltier elements, which provide local temperature control for a 36-cm^2^ plate. An optic fibre is integrated in the plate, flush to its surface, which allows for the continuous monitoring of skin blood flow via Laser Doppler Flowmetry (LDF). The thermal probe is mounted on a frame with an integrated strain gauge to estimate the force applied to the stimulator. When applied to the skin, the integrated device allows for the manipulation of local skin temperature (range: 0°C to >50°C; variable temperature rates under PID control), applied pressure and the concurrent monitoring of blood flow.

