**Fig 2 pone.0303342.g002:**
[figure not shown]
Standardise pressure protocol delivered over the sacrum. The thermal probe will be used to deliver a standardised 60mmHg pressure protocol to evoke pronounced tissue ischaemia under 3 thermal conditions, i.e. a control skin temperature evoking no cooling (i.e. 38°C) and two cooling temperatures of 24°C and 16°C. During the protocol, a series of non-invasive measurements will be conducted [i.e. skin blood flow via LDF; inflammatory biomarker sampling from skin sebum; structural and functional imaging via Optical Coherence Tomography (OCT); perceptual assessment of subjective thermal sensation, comfort, and acceptance] at different time points (identified in the diagram by ↑).

The protocol consists of three phases; i) a 10-minute baseline stabilisation with minimal pressure (17.5 mmHg (2.3 kPa)), ii) 45-minute loading phase (60 mmHg/7.9 kPa [15)), and iii) a 20-minute minimal pressure phase (same as baseline). Skin blood flow will be measured continuously throughout the three phases of the protocol via Laser Doppler Flowmetry (Moor Instruments, moorVMS-LDF laser Doppler monitor, UK) with perceptual responses measured at predetermined intervals during the protocol (Fig 2). During the baseline phase in all conditions, the temperature probe will be set to 34 °C. On starting the loading phase, the thermal probe will be loaded with a 2 kg weight to elicit an equivalent pressure of 60mmHg (7.9 kPa) at the probe interface. The initial 5-mintues of the loading phase will serve as a further baseline measurement for the pressure protocol, to delineate the effects of 60mmHg loading alone on microvascular responses. To this end, once the load is applied to the sacrum, the probe temperature will remain at 34 °C. Following this, the temperature probe will be set to the target temperature for the specific testing session, either 38 °C (Δ13.7 °C/min), 24 °C (Δ11.3 °C/min), or 16 °C (Δ9.2 °C/min) and will be maintained at such temperature until the end of the session.

Upon completion of the loading phase, the thermal probe will be unloaded (Fig 2) whilst maintained in position over the sacrum, to allow skin tissue blood flow reperfusion (which will be continuously monitored by via LDF). The minimal loading phase (comparable to the initial 10-minute baseline phase) will last for 20 minutes, after which the thermal probe will be removed to allow for image acquisition via OCT and a final sampling of skin sebum over the sacrum.

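### For biomarkers and OCT, post-hoc temperature comparisons depend on a main effect that carries only half of any post-exposure effect; the full effect lies in temperature × time, which the post-hoc rule does not mention

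*Protocol article*

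**What the plan says.** **Outcome and model.** The Statistical analyses section says of the secondary outcomes that "these will be within- and between-subject changes in biomarkers’ expression, skin structural and biophysical properties", together with thermal perceptions, are to be studied by temperature, group and "time (i.e. varying levels depending on variables’ sampling rate". The analysis covers the "independent and interactive effects of pressure and stimuli temperature, time, and participant group by means of a 3- way mixed model ANOVA", with Friedman as the non-parametric alternative.

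**Follow-up rule.** In the same section: "Post-hoc analyses will be performed between pressure stimuli temperatures, time, and participant groups based the presence of main effects", using Tukey's test. Interactions are not named as a trigger.

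**Sampling.** Under Experimental procedures, before the probe is placed: "First, structural, and functional imaging of the skin of the sacral skin using Optical Coherence Tomography (OCT) will be performed", and then "This will be followed by sampling of skin sebum at the sacrum for subsequent biomarker analysis". At the end of the session, "the thermal probe will be removed to allow for image acquisition via OCT and a final sampling of skin sebum". The Skin imaging section likewise describes OCT as done before and after the manipulation. The text therefore gives two samples per session for both outcomes.

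**Temperature before the contrast starts.** "During the baseline phase in all conditions, the temperature probe will be set to 34 °C". The probe stays at 34 °C for the first 5 minutes of loading and only then moves to 38, 24 or 16 °C.

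**The concern.** A pre-to-post change gives one value per session, so time has no levels and the model is 2-way. A 3-way model of two samples must use raw values, with the pre-exposure sample as a level of time. The article does not say this outright, but no other reading lets the model run for biomarkers and OCT.

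On that reading the temperature marginal mean is the average of a sample that cannot show a temperature effect and one that can. The pre-session value could remove noise as a covariate; here it dilutes the outcome. Because the post-hoc rule looks to main effects, the diluted term decides whether temperatures are compared and what those comparisons estimate. An effect visible in temperature × time, without a temperature main effect, has no stated route to pairwise comparison. The inflammatory and structural responses to cooling are part of the first aim in the Introduction, so this matters even though they are secondary.

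**Working it through.** **The plan's own figure.** The article gives no power figure for any secondary outcome. Its minimum of 18 per group is for peak hyperaemia (within-between interaction, f = 0.4), a different outcome and a different term, so it cannot serve as a check here. The numbers of participants are used: 35 per group planned (N = 105) and 18 per group minimum (N = 54).

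**Inputs from the article.** Three temperatures, three groups, one pre- and one post-exposure sample per session, α = 0.05.

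**Assumptions (not in the article).**
- Value = person + session + error, with session variance s² and error variance e², scaled so that s² + e² = 1.
- r = s²/(s² + e²), the within-session pre-post correlation once the person effect is removed, taken as 0, 0.5 and 0.7.
- Temperature effect only on the post sample: 0, 0.25 and 0.5 within-person SD at 38, 24 and 16 °C, the same in every group.

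**Step 1: what each term estimates (16 versus 38 °C, d = 0.5).**
- Main effect: (0 + d)/2 = 0.25.
- Temperature × time, which with two samples is the same test as temperature on post minus pre: d − 0 = 0.50.
- Post adjusted for pre: 0.50.

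**Step 2: noncentrality.** The centred effects are −0.25, 0 and 0.25, so SS = 0.0625 + 0 + 0.0625 = 0.125. For N = 105, N·SS = 13.125; for N = 54, it is 6.75.
- Main effect: the variance of (pre + post)/2 is s² + e²/2 = (1 + r)/2 and the effects are halved, so λ = (N·SS/4)/((1 + r)/2) = N·SS/(2(1 + r)).
- Change: the variance is 2e² = 2(1 − r), so λ = N·SS/(2(1 − r)).
- Adjusted: the residual variance is 1 − r², so λ = N·SS/(1 − r²).

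**Step 3: power.** Noncentral F with 2 and 2(N − 3) degrees of freedom (204 or 102), ignoring the one degree of freedom the covariate uses.

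| N | r | λ main / change / adjusted | Main effect | Temperature × time | Post adjusted for pre |
|---|---|---|---|---|---|
| 105 | 0 | 6.56 / 6.56 / 13.13 | 62% | 62% | 91% |
| 105 | 0.5 | 4.38 / 13.13 / 17.50 | 44% | 91% | 97% |
| 105 | 0.7 | 3.86 / 21.88 / 25.74 | 40% | 99% | 99.7% |
| 54 | 0 | 3.38 / 3.38 / 6.75 | 35% | 35% | 62% |
| 54 | 0.5 | 2.25 / 6.75 / 9.00 | 24% | 62% | 76% |
| 54 | 0.7 | 1.99 / 11.25 / 13.24 | 22% | 85% | 90% |

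**Step 4: ratios.**
- Main effect against change: the ratio of λ is (1 − r)/(1 + r), that is 1.00, 0.33 and 0.18 at r = 0, 0.5 and 0.7.
- Adjusted against main effect: the ratio of z-statistics is √(2(1 + r)/(1 − r²)) = √(2/(1 − r)), that is 1.4, 2.0 and 2.6.

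**Check by simulation** (35 per group, 1,500 runs per setting). The mean estimated 16 versus 38 °C effect was 0.25 for the main effect and 0.50 for the other two. Power at r = 0, 0.5 and 0.7 was 61%, 43% and 38% for the main effect, and 90%, 97% and 99.6% for the adjusted analysis, in line with the table.

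**The case against.** The strongest reply is that the planned model already contains the right test. It covers interactive effects, and temperature × time is the change-score analysis with the full d. Describing pre/post data as changes by temperature, time and group is ordinary usage, and an analysis plan may name the deciding term. Much of this stands. A reader might infer that the whole analysis halves the temperature effect; it does not, since only the main effect is halved. What the reply leaves untouched is the follow-up rule, which the article does state and which names main effects alone.

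Three further readings are tempting and are not supported:
- **Most of the power is lost.** This depends on r and on the effect size, and the article gives neither for secondary outcomes. At r = 0 the main effect loses nothing against change scores, and about a third against the adjusted analysis (62% against 91%). Large effects survive: at f = 0.4, stated only for the primary outcome, halving f with the SD unchanged and an assumed correlation of 0.5 leaves power of 0.90 at N = 54 and 0.996 at N = 105.
- **Reported secondary confidence intervals will be halved.** The Statistical analyses section ties 95% intervals to peak hyperaemia only.
- **Perceptual ratings are diluted by a known amount.** Ratings taken at 34 °C would dilute a temperature main effect in the same way, but the rating schedule is in Fig 2, which is not shown, so the amount cannot be stated. Time is a legitimate factor for these ratings, and the discomfort thresholds come from separate per-participant regressions.

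**Conclusion.** The point holds for biomarkers and OCT in this form: the term that triggers temperature comparisons estimates half of any post-exposure effect, while the term carrying the full effect is tested but does not trigger follow-up. The halving follows from the sampling scheme, given that the pre-exposure sample is a level of time. That is inferred, but it is the only way time can enter a model of two samples.

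The size of the power loss is conditional. With the assumed effects and 35 per group, the main effect has 40% to 62% power over r = 0 to 0.7, against 62% to 99% for temperature × time and 91% to 99.7% for the adjusted analysis. The gap between the two planned terms is nil at r = 0 and widens as r rises. For perceptual ratings the direction is the same and the size unknown. The primary outcome is not affected by this: it is normalised to baseline and its 2-way model has no time factor.

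**What to change.** - **Biomarkers and OCT:** make the temperature comparison on the post-session value, with that session's pre-session value as covariate and temperature, group and their interaction as factors. At minimum, name temperature × time as the deciding test.
- **Post-hoc rule:** base temperature comparisons for these outcomes on that test and its adjusted means (or mean changes), not on the temperature main effect.
- **Perceptual ratings:** keep ratings taken at 34 °C out of the temperature main effect, for example by using their mean as a covariate and counting as time levels only ratings taken after the probe has reached the session temperature.

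The cost is a change of analysis wording and one degree of freedom for the covariate. No new data are needed, because the pre-session samples are already part of the protocol.
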